Event-Related Potentials laterality is still a controversy. Some experimental paradigms have found a right-hemispheric dominance for emotional processing, regardless of the valence (result in accordance with the Right-Hemispheric Hypothesis) (Godfrey and Grimshaw, 2016; Charpentier et al., 2018). The left lateralization for the processing of positive emotions and higher right hemispheric neuronal activity for negative emotions (i.e., the Valence Theory) has also been observed, without denying the possibility of the mutual coexistence of both phenomena (Wyczesany et al., 2018). Although a sparse literature relative to the ERPs analysis underlying the processing of emotional prosody in autistics, a reduced modulation of the neuronal activity by emotions and a lack of hemispheric lateralization has been observed in this population (Lindström et al., 2016, 2018; Charpentier et al., 2018). Remarkably, in a study focused on the processing of emotional words by autistic adults and their corresponding TD controls, the amplitude of the LPP for positive or negative versus neutral words processing did not reach significance for autistic participants. In contrast, higher amplitude were observed for emotional versus neutral stimuli in the TD sample, and group differences were identified for negative versus neutral words (Lartseva et al., 2015).

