#### MESD Speech Corpus Stimuli

Words for speech utterances will be selected from two sources: the single-word corpus from the INTERFACE for Castilian Spanish database (Hozjan et al., 2002; Emotional Speech Synthesis Database, 2012), and the Madrid Affective Database for Spanish (MADS; Hinojosa et al., 2016a, b). For the creation of the MESD, the 24 isolated words that composed the INTERFACE database will be selected and will repeat across emotions. Words from MADS will be selected based on grammatical class and ratings for valence, arousal, qualitative emotion (anger, disgust, fear, happiness, neutral, and sadness), concreteness, familiarity, frequency, and subjective age of acquisition. Specifically, all words will be nouns or adjectives. Their subjective age of acquisition will be strictly under 9-year-old. Valence and arousal ratings of neutral words will be strictly greater than 4 but lower than 6 (on a 9-point scale), whereas emotional words will be selected to have valence and arousal ratings ranging from 1 to 4, or from 6 to 9. A rating superior to 2.5 (on a 5-point scale) for a particular emotion will allow the qualitative categorization of the word into anger, disgust, fear, happiness, or sadness. Words from MADS will be selected in order to ensure that they will be matched for concreteness, familiarity, and frequency ratings. Words selection will be carried out separately for male, female, and mean ratings for all subjects.

Statistical analysis will be used to guarantee that frequency, familiarity, and concreteness are matched between neutral, fear, disgust, happiness, sadness, and anger words. Values obtained for each of these parameters will be analyzed separately with one-way ANOVAs. Normality and homogeneity will be assessed using Shapiro–Wilk and Bartlett tests, respectively. In case of non-parametric distribution of the data, Kruskal–Wallis test will be applied. *Post hoc* tests will be used to statistically assess specific differences (Tukey after ANOVA, Wilcoxon tests with *p*-value adjustment by Holm method after Kruskal–Wallis). In case of significant differences between emotions, outlier values will be identified, and corresponding words will be eliminated until reaching no difference for all of three parameters. We will consider outliers all ratings for frequency, familiarity or concreteness outside the range defined by percentiles 2.5 and 97.5.

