Mean and standard deviation scores for male, female, children, and all together ratings will be calculated for each word. For culture comparisons, one-way ANOVAs will be conducted for each emotion and variable separately on words qualified as referring to a specific emotion in both cultures. Sample size estimation was calculated with G^∗^Power software version 3.1.9.7 (Faul et al., 2007) for Cohen’s d effect size index of 0.8, and statistical significance set at *p* < 0.05. Results indicated that 34 participants in each category (adult male, adult female, and child) would be enough to provide an estimated power of 0.90. For emotion comparisons in Mexican ratings, values obtained for each variable will be analyzed separately with one-way ANOVAs. Normality and homogeneity will be assessed using Shapiro–Wilk and Bartlett tests, respectively. In case of non-parametric distribution of the data, Kruskal–Wallis test will be applied. *Post hoc* tests will be used to statistically assess specific differences (Tukey after ANOVA, Wilcoxon tests with *p*-value adjustment by Holm method after Kruskal–Wallis). In case of cross-cultural differences, outlier values from both Spanish and Mexican ratings will be identified, and corresponding words will be eliminated until reaching no cultural difference, and no emotional difference for Mexican ratings for all of three parameters (familiarity, frequency, and concreteness). We will consider outliers all ratings for frequency, familiarity or concreteness outside the range defined by percentiles 2.5 and 97.5. The final speech corpus from MADS will be composed of 144 words (24 per emotion), so that the final MESD corpus will be composed of 48 words per emotion (24 from INTERFACE and 24 from MADS).

Forty Mexican participants of each category (adult male, adult female, and child) will voluntarily answer the questionnaires. Adults will be aged between 19 and 35 years old, and children between 9 and 11 years old. They will be excluded if they have been diagnosed with any pathology that affects emotional behavior. They will be included if that have grown up in Mexico in a cultural Mexican environment (Mexican academic education and family environments). Participants will be recruited via public posted on Tecnologico de Monterrey, Campus Monterrey.

In all cases, significance will be set at *p* < 0.05. Statistical analysis will be performed with R software (R Foundation for Statistical Computing, Vienna, Austria).

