#### Passive Oddball Paradigm

Emotional and neutral words uttered by human voices recorded in stage 1 and synthesized voices created in stage 2 will be displayed to the participant. During the EEG recording, participants will sit on an armchair while watching a silent movie and will be instructed to pay no attention to the auditive stimuli. To facilitate the comparison of naturalness levels, six stimulus blocks will be created, each containing 600 stimuli corresponding to one of the five levels, or the human voice. Each block will consist of 480 frequently presented neutral-uttered standard stimuli (80%), and occasional 24 anger (4%), 24 disgust (4%), 24 fear (4%), 24 happiness (4%), and 24 sadness (4%) deviant stimuli. Standard and deviant stimuli will be equally uttered with a male, woman, or child voice. The stimuli will be presented pseudo-randomly with deviant stimuli being preceded by at least two standard stimuli. Each participant will listen to three blocks for an approximatively 30-min task. The stimulus sequences for each block will be fixed, and the order of blocks will be counterbalanced and randomized between participants. The stimulus onset asynchrony will be of 1,300 ms. The stimuli will be presented at 60 dB via the Shure SRH1840 audio headset that has a flat response frequency response in order to accurately reproduce the input audio signal. Autistic participants will be accompanied by their parent if necessary.

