##### Behavioral assessments

At pre- (1st session), mid- (7th session), end- (13rd session), and follow-up sessions (2 and 6 weeks after the end of the intervention), participants will be asked to answer the following behavioral task. It will consist of one block of stimulus pairs containing 244 pairs that will be presented at 60 dB via the Shure SRH1840 audio headset. The stimulus pair will be composed of either identical stimuli (50%; two neutral stimuli), or different stimuli [one neutral and one of the emotional deviants (50%; anger (10%), disgust (10%), fear (10%), happiness (10%), or sadness (10%)]. Fifty percent of pairs that contain a deviant stimulus will be composed of 1 neutral followed by 1 emotional stimulus, and 50% will be composed of 1 emotional followed by 1 neutral stimulus. Word pairs will be equally uttered with a male, woman, or child voice. The within-pair stimulus onset asynchrony will be 1,300 ms, and the between-pair stimulus onset asynchrony will be 2,600 ms. The order of stimulus pairs will be randomized between participants, but the stimulus sequence will be fixed. During this approximately 20-min task, participants will have to answer by pressing previously instructed keys on a laptop keyboard, if the emotional prosody of both stimuli of each pair will be the same or different. If they choose different, they will have to mention the emotion conveyed by the deviant (anger, disgust, fear, happiness, or sadness). Reaction times and correct/incorrect answers will be recorded. To make sure that the participant understands the task, three training trials will be presented before the test. Autistic participants will be accompanied by their parent if necessary.

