##### EEG assessments

After behavioral assessment at pre- (1st session), mid- (7th session), end- (13rd session), and follow-up sessions (2 and 6 weeks after the end of the intervention), EEG data will be recorded while participants listen to a passive oddball paradigm. Emotional and neutral words uttered by human voices recorded at Stage 1 will be displayed to the participant. During the EEG recording, participants will sit on an armchair while watching a silent movie and will be instructed to pay no attention to the auditive stimuli. One stimulus block containing 1,200 words will be presented for an approximately 20-min paradigm. It will consist of 960 frequently presented neutral-uttered standard stimuli (80%), and occasional 48 anger (4%), 48 disgust (4%), 48 fear (4%), 48 happiness (4%), and 48 sadness (4%) deviant stimuli. Standard and deviant stimuli will be equally uttered with a male, woman, or child voice. The stimuli will be presented pseudo-randomly with deviant stimuli being preceded by at least two standard stimuli. The stimulus sequence will not vary between participants. The stimulus onset asynchrony will be of 1,300 ms. The stimuli will be presented at 60 dB via the Shure SRH1840 audio headset. Autistic participants will be accompanied by their parent if necessary.

Electroencephalographic recording and processing will follow the same methodology as the one described in section “EEG Recording and Processing.”

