## Discussion

This project of investigation aims to fulfill three main gaps of the current scientific literature. First, acoustic parameters from Castilian and Mexican Spanish will be analyzed in order to validate a newly formed emotion speech database for Mexican Spanish and to highlight cross-cultural differences in the way of expressing emotions by prosody. The first issue was to determine which acoustic features should be considered to optimize the distinction from one emotion to another. As no reliable set of acoustic features exists yet, a literature review of prosodic emotional speech parameters was conducted. MFCC coefficients were the most usually extracted features for machine learning applications. This analysis consists of computing the log values of a linear cosine transform of spectral parameters on a Mel scale, thus considering the human particularities of frequency responses (Caballero-Morales, 2013). Other recurrent spectral features were the pitch (fundamental frequency), formants, jitter, shimmer and harmonics-to-noise ratio (Swain et al., 2018). Formants are high-energy frequencies acoustic resonances of the vocal tract (Gelfand, 2009). They are generally labeled F1, F2, F3, and so on, from the lowest formant to the highest: the first three- formants are usually extracted for emotions discrimination (Kamińska, 2019). Jitter and shimmer refer to a period-to-period fluctuation of the pitch and the energy, respectively (Arruti et al., 2014). The harmonics-to-noise ratio considers the energy of the harmonics according to the one of other frequencies. It is directly correlated to the voice quality according to breathiness and roughness and is a principal component to characterize human voices (Arruti et al., 2014). The energy, intensity and rate were other features commonly used for emotional prosody recognition (Swain et al., 2018). Therefore, it is suitable to extract those acoustic parameters for the present work and predict high accuracy in emotions discrimination and classification. However, previous studies have also highlighted the influence of linguistic parameters on emotions processing (Méndez-Bértolo et al., 2011; Palazova et al., 2011; Hinojosa et al., 2014). Therefore, it is necessary to supervise linguistic values, for all stimuli to be nouns and adjectives, valence, arousal, and emotional category to be in accordance with prosody, and frequency, concreteness, and familiarity matched between emotions, so that the unbiased allocation of prosody during recordings may be ensured. Controlling for these factors will add reliability to our database and enrich the current available material, as previous works for Spanish emotional utterances did not systematically control for linguistic features (Caballero-Morales, 2013; Hinojosa et al., 2016a, b; Pérez-Espinosa et al., 2020).

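### For the MADS share of the stimuli, the behavioural and ERP measures do not separate prosody from word meaning

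*Protocol article*

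**What the plan says.** The corpus has two halves. In the section on MESD Speech Corpus Stimuli, "the 24 isolated words that composed the INTERFACE database will be selected and will repeat across emotions", so for these words meaning gives no clue to the emotion. The MADS words are selected by the emotion of their meaning: "A rating superior to 2.5 (on a 5-point scale) for a particular emotion will allow the qualitative categorization of the word". Neutral MADS words must have valence and arousal strictly between 4 and 6. Emotional ones must lie in 1 to 4 or 6 to 9. The same section fixes the composition: "the final MESD corpus will be composed of 48 words per emotion (24 from INTERFACE and 24 from MADS". Matching across emotions covers frequency, familiarity and concreteness only. The Discussion confirms that the link between meaning and prosody is intended, with "valence, arousal, and emotional category to be in accordance with prosody".

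The test stimuli come from this material. For Stage 2, "Emotional and neutral words uttered by human voices recorded in stage 1 and synthesized voices created in stage 2 will be displayed". For Stage 3, "Emotional and neutral words uttered by human voices recorded at Stage 1 will be displayed to the participant". The Behavioral assessments section says "The stimulus pair will be composed of either identical stimuli (50%; two neutral stimuli), or different stimuli". It names no corpus and sets no rule on the word used within a pair. The child judges whether the prosody of the two items is the same and, after answering *different*, names the emotion.

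Corpus appears as a factor only in the Stage 1 acoustic analysis (Sound Processing and Analyses). It is absent from the Stage 2 ERP models and from the Stage 3 behavioural and ERP models.

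**The concern.** Stages 2 and 3 are about emotional prosody. If an emotional item is also a word whose meaning carries that emotion, a correct answer, a faster response or a larger difference wave need not come from prosody. The neutral and emotional rating bands exclude each other, so every MADS emotional item differs from a neutral MADS item in word and in meaning as well as in prosody. The words have a subjective age of acquisition under 9 years, so children of 9 to 11 should know them.

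Two kinds of contrast are most exposed:

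- **Autistic versus TD children.** The two groups may differ in how they respond to emotional meaning. The Introduction cites a study of autistic adults hearing or reading emotional words (the modality is not given) in which "group differences were identified for negative versus neutral words" for the LPP. This makes the concern plausible. It does not measure it in children listening passively.
- **Groups 1 and 2 versus Group 3.** The Social Stories describe and compare emotions verbally. Trained children could improve on word meaning with no gain in prosody.

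**Working it through.** **Inputs from the protocol**

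- Six prosodies, five of them emotional; 24 INTERFACE and 24 MADS words per emotion (MESD Speech Corpus Stimuli).
- 244 pairs, 50% same and 50% different, 10% per emotion; five emotion labels (Behavioral assessments).
- Deviants per emotion: 24 in a Stage 2 block, 48 in the Stage 3 block. Standards: 480 and 960.
- Three voice types.

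**Input not given:** the share *s* of *different* pairs built on MADS words. It is varied from 0 to 1.

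**1. The plan's own counts.** 24 + 24 = 48 words per emotion; 6 × 24 = 144 MADS words; 6 × 48 = 288 utterances per voice type. All agree with the text.

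**2. Share with congruent meaning.** Emotional MADS utterances per voice type: 5 × 24 = 120. All emotional utterances: 5 × 48 = 240. So 120/240 = 50% of the emotional utterances, or 120/288 = 41.7% of all utterances.

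**3. Same/different score of a listener who uses meaning and no prosody.** There are 244 × 0.5 = 122 same pairs and 122 different pairs. This listener answers *same* to two neutral items (correct), *different* when a word has emotional meaning (correct), and *same* to an INTERFACE pair, where meaning gives no cue (wrong if the pair is a different one).

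Score = (122 + *s* × 122) / 244. Share of deviants that can be named from meaning = *s*.

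| *s* | Same/different score | Named from meaning |
|---|---|---|
| 0 | 122/244 = 50% | 0% |
| 0.25 | 152.5/244 = 62.5% | 25% |
| 0.5 | 183/244 = 75% | 50% |
| 1 | 244/244 = 100% | 100% |

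Always answering *same* gives 50%, and guessing one of five labels gives 20%. The table treats meaning as a perfect cue, so each row is an upper limit for its *s*.

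**4. Would the INTERFACE words be enough?** 24 words × 3 voice types = 72 recordings per emotion. Needed per emotion: 24 (Stage 2 block), 244 × 0.10 = 24.4 nominally (pair task), 48 (Stage 3 block). The set suffices.

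**5. Repetition of neutral standards.** Stage 3 block: 960/72 = 13.3 plays per recording, against 960/144 = 6.7 with both halves. Stage 2 block: 480/72 = 6.7, against 480/144 = 3.3.

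**6. Speaker.** Under Emotions Classification, the final database takes, for each emotion, the speaker (for children, the pair of speakers) with the best F-score. Neutral and angry items of one voice type can therefore come from different people. Matching on voice type alone would leave a change of speaker within a pair.

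**The case against.** A condensed article may leave stimulus lists to a fuller document, and no section says that pairs or sequences mix different words. INTERFACE words allow same-word pairs throughout. This stands: the point is that the corpus and the word are not restricted, not that they are known to be mixed. It does not remove the concern. Where the authors restrict a corpus they say so (INTERFACE words for the cultural comparison, MADS neutral words for the text-to-speech files), and the stated models have no corpus term.

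A reader might infer that a child could reach about 99% simply by noticing a change of word. That needs three unstated conditions together: half of the *different* pairs are MADS, INTERFACE pairs are drawn at random, and identical means one recording played twice. If *same* pairs are two different neutral words, the rule fails. In the oddball, if words vary at all, the standards vary too, so a word change does not mark a deviant. What remains there is the response to meaning.

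A reader might also infer that the trial cannot attribute any result to prosody. The protocol does not support this:

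- Groups 1 and 2 are randomised and receive the same intervention apart from the voice, so verbal teaching is balanced between them.
- The Stage 2 levels are edits of the same recordings, applied alike to all emotions, so meaning does not vary with level.
- ASRS does not use these stimuli.

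Finally, congruent MADS words have a stated purpose: to avoid bias in how actors allot prosody during recording. That justifies them for building the database, not for testing prosody.

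**Conclusion.** The concern holds for the MADS share of the stimuli. Half of the emotional words match the prosody in meaning by design, nothing in the task or oddball sections limits or balances them, and the stated models cannot separate the two corpora. Followed as written, the plan yields accuracy, reaction-time and deviant-minus-standard measures that do not isolate prosody.

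The size depends on an unstated share: 50% to 100% on same/different and 0% to 100% on naming for a listener using meaning alone. The illustration of 75% and 50% assumes that half of the *different* pairs are MADS. It also assumes that the pair task draws on the Stage 1 recordings, which its section does not say.

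Autistic versus TD comparisons and Groups 1 and 2 versus Group 3 are the most exposed. Randomised contrasts among Groups 1 to 3 still estimate an intervention effect, but not one specific to prosody. Group 1 versus Group 2, the comparison of Stage 2 levels and ASRS are largely unaffected.

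**What to change.** Before the stimulus lists are fixed, state that the same/different pairs and both oddball sequences use only the 24 INTERFACE words. Within each pair, use the same word and the same speaker in both members, not only the same voice type. In the oddball sequences, use the same words for standards and deviants. Keep the MADS words for the database and the acoustic work.

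The recordings are already planned. Each adult utters the INTERFACE words in all six prosodies, and so does each of the four children assigned to that corpus (24 × 6 = 144 utterances), so one speaker per voice type can supply every emotion. The costs are fewer distinct words, about twice as many plays of each standard (about 13 against 7 in a Stage 3 block, at each of five assessments), and giving up the choice of speaker by emotion for the test stimuli.

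If MADS words are kept, add Corpus as a factor in the behavioural and ERP models and name the INTERFACE subset as the test of prosody, with the same word and speaker rule inside that subset. This keeps more varied material but leaves fewer deviants for the key test: with an equal split (an assumption), 12 of 24 per emotion in a Stage 2 block and 24 of 48 in the Stage 3 block.

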##### Statistical analysis on behavioral data

Group comparisons of reaction times will be conducted by a Group × Stimulus (neutral, anger, disgust, fear, happiness, or sadness) repeated measures ANOVAs on each assessment session separately. Time comparisons will be conducted by Assessment Session × Stimulus on each group separately. Normality of reaction times will be assessed by Shapiro–Wilk test. In case of non-parametric distribution of the data, a transformation will be applied. Mauchly’s test of sphericity will be used to evaluate homogeneity of variances and co-variances. In case of violation of sphericity, a Greenhouse-Geisser correction will be applied in order to test main effects significance. Post-hoc comparisons will be conducted to assess specific differences (Tukey procedure).

Group comparisons of number of correct answers will be conducted by one-way ANOVAs for each deviant and assessment session separately. Time comparisons (between assessment sessions) will be tested by one-way ANOVAs on number of correct answers for each deviant and each group separately. Normality and homogeneity of variances will be assessed by Shapiro–Wilk and Bartlett tests, respectively. In case of non-parametric distribution of the data, Kruskal–Wallis test will be applied. *Post hoc* comparisons will be conducted to assess specific differences (Tukey after ANOVA, Wilcoxon tests with *p*-value adjustment by Holm method after Kruskal–Wallis).

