This project of investigation might encounter some pitfalls and unexpected results. Non-professionalism of actors recruited for emotional recordings during Stage 1 may affect the reliability of required prosodies. Nevertheless, the number of volunteers will be increased in order to generate four times more utterances than necessary to enable the selection of best actor participants. Furthermore, emotion recognition accuracy will be validated by supervised learning algorithm to ensure the quality of emotion discrimination based on acoustic features. Stage 2 aims to explore emotional recognition impairments in autism triggered by naturalness of human voices. We expect to observe a diminution of the amplitude of ERPs in the autistic population as a reflect of decreased attentional, sensorial, and cognitive emotional processing (Lartseva et al., 2015; Lindström et al., 2016, 2018). The autistic condition may also be characterized by hemispheric lateralization anomalies due to lateralized compensatory brain activity (Subbaraju et al., 2018). Impairments are expected to fade with the decreasing naturalness of voice stimuli. However, in the opposite case, no effect of naturalness on neural emotional processing by autistic children would be an evidence that the modulated acoustic parameters would not participate to autistic impairments. In the latter situation, or in case of enhancement of autistic impairments triggered by naturalness modulations, the acoustic edition of the stimuli will be reconsidered. Finally, Stage 3 expects the implementation of less natural voices in a robot-based intervention with the aim of improving emotion detection by autistic children. The 2-week intervention may imply a high rate of withdrawals whereas the sample size needed is relatively high. However, upon completion, we expect the intervention to trigger a reduction of autistic impairments (reduction of symptomatology, higher EEG activity, higher behavioral accuracy for emotion discrimination: smaller reaction times, and higher correct answers at end- and follow-up assessments).

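### In the Stage 3 pair task half of the emotional pairs can be answered from the first word; the reaction-time models ignore pair order, so the neutral and emotion levels are not comparable

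*Protocol article*

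**What the plan says.** The protocol article, under Outcome Measures, Behavioral assessments, sets the size of the task: "It will consist of one block of stimulus pairs containing 244 pairs". Pairs are "either identical stimuli (50%; two neutral stimuli), or different stimuli", and the different half is "one neutral and one of the emotional deviants (50%; anger (10%), disgust (10%), fear (10%), happiness (10%), or sadness (10" per cent). On order it says "Fifty percent of pairs that contain a deviant stimulus will be composed of 1 neutral followed by 1 emotional stimulus", and of the remainder that "50% will be composed of 1 emotional followed by 1 neutral stimulus". On timing: "The within-pair stimulus onset asynchrony will be 1,300 ms, and the between-pair stimulus onset asynchrony will be 2,600 ms".

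The child presses a key for same or different prosody and, after answering different, names the emotion of the deviant. Reaction time and correctness are recorded. The article gives neither the point from which reaction time is measured nor the window in which a key press counts.

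Under Statistical analysis on behavioral data the model is: "Group comparisons of reaction times will be conducted by a Group × Stimulus (neutral, anger, disgust, fear, happiness, or sadness) repeated measures ANOVAs", run at each assessment session. Time comparisons use Assessment Session × Stimulus within each group. Pair order is not a factor, a stratum or a restriction in either model.

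The Discussion lists the expected signs of benefit, among them "smaller reaction times, and higher correct answers at end- and follow-up assessments".

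**The concern.** A same/different task is meant to time a comparison of two words. Here an emotional first word makes the comparison unnecessary: the pair must be different, and the emotion to be named has already been heard. After a neutral first word the child has to wait for the second. The two orders thus become decidable at different moments, and the planned models put them together within each emotion. The neutral level contains only pairs of the waiting kind.

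Two things are at stake. First, any contrast of neutral with an emotion in the Stimulus factor partly reflects when the pair could be decided, not how quickly prosody was processed. Second, shorter reaction time is named as a sign of improvement. A child who learns over repeated sessions that an emotional first word settles the answer will look faster for that reason alone.

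**Working it through.** **Inputs** (all from Behavioral assessments): 244 pairs; 50% identical, all neutral-neutral; 50% different, 10% per emotion; different pairs split 50/50 by order; word onsets within a pair 1,300 ms apart. The plan states no figure of its own on this point, so there is none to reproduce.

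**1. Counts**
- Neutral-neutral: 244 × 0.5 = 122.
- Neutral then emotional: 244 × 0.5 × 0.5 = 61.
- Emotional then neutral: 244 × 0.5 × 0.5 = 61.
- Decidable only at word 2: 122 + 61 = 183.

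**2. What the first word tells the child**
- P(different | first word emotional) = 61/61 = 1.
- P(different | first word neutral) = 61/183 = 0.33.
- A child who classifies word 1 correctly and ignores word 2 is right on 61 + 122 = 183 pairs: 183/244 = 75% on same/different.

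**3. Effect on the neutral-versus-emotion contrast.** Let L be the processing time after the decisive word, equal for all pair types, with the response given at the decision point.

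| Clock starts at | Emotional-first | Neutral-first | Emotion mean | Neutral-neutral | Emotion minus neutral |
|---|---|---|---|---|---|
| Word 1 | L | L + 1,300 | L + 650 | L + 1,300 | −650 ms |
| Word 2 | L − 1,300 | L | L − 650 | L | −650 ms |

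Under free responding, the choice of clock start does not remove the difference.

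**4. Partial use of the cue.** Let s be the share of emotional-first pairs answered at word 1, the rest being answered as if decided at word 2. The emotion mean shifts by 0.5 × 1,300 × s = 650·s ms. The documents give no value for s, so a range is shown:
- s = 0.10: 65 ms
- s = 0.25: 163 ms
- s = 0.50: 325 ms
- s = 1: 650 ms

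**5. Group and session contrasts.** The order mix is the same in every group and session. The difference in emotion means between two groups or sessions caused by the cue is 650 × (s₁ − s₂). It is zero when s is equal, and 65, 163 or 325 ms when s differs by 0.10, 0.25 or 0.50, again only if early key presses are recorded.

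**6. If keys count only after word 2.** An early answer cannot be recorded, but it can be prepared. The two orders then differ by a preparation advantage that the documents give no means of sizing.

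**The case against.** **The 1,300 ms gap depends on a response rule that the article does not state.** The task asks for a judgement on both words, which fits a response after the second. This stands: 650 ms is an upper figure for the emotion-versus-neutral gap, not an expected one. Clock start and response window are details that a condensed article may leave to a fuller document, and their absence is not the complaint. The pair composition and the model factors are both fixed in the text, and together they make the levels unlike under either rule.

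**Order is balanced.** A reader might infer that pooling the orders biases the treatment comparison. The documents do not support that. The 50/50 split applies to all groups and sessions, so pooling alone cancels in those contrasts, and bias needs unequal use of the cue. That is plausible across five assessments, and for Groups 1 and 2 against Group 3, because the first two practise naming the emotion of utterances in 12 sessions (six a week for two weeks). For Group 1 against Group 2, the comparison meant to evaluate the synthesized voices, both groups receive the same training apart from the voice, and nothing in the article suggests that cue use would differ.

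**Using the cue still takes prosody recognition.** To answer early and correctly, the child must recognise emotion in one word, which is the trained skill. This also stands: a shorter time through the cue is not empty of skill, but it does not time the two-word comparison.

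**No false-positive rate can be given.** One might wish to turn a shift of 163 ms into a standardised effect or an error rate. That needs a reaction-time SD, a response rule and a pattern of cue use across children, none of which the article gives. No such rate is claimed here.

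**Conclusion.** The point holds for the Stimulus factor. As planned, the neutral level (second-word decisions only) is not comparable with the emotion levels (half first-word, half second-word decisions). At equal processing speed the emotion means are up to 650 ms earlier than neutral if children respond at the decision point. If responses are accepted only after word 2, they are earlier by a smaller, unknown amount.

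For group and session contrasts the point is conditional: a bias of 650 ms times the difference in early-answer share, under free responding, and none when the share is equal. It is a plausible risk for session contrasts and for Groups 1 and 2 against Group 3. The documents give no reason to expect it for Group 1 against Group 2. It concerns reaction time, one of several Stage 3 outcomes, and deserves correction because separating the orders is cheap.

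**What to change.** In Statistical analysis on behavioral data:

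- Base the main reaction-time analysis on neutral-first emotional pairs and neutral-neutral pairs, timed from the onset of the second word. All of these become decidable at the same moment.
- Analyse the emotional pairs with Order (emotional-first or neutral-first) as a within-child factor across the five emotions, or report emotional-first pairs separately. Order cannot be crossed with the neutral level, which has only one order, so it should not simply be added to the six-level model.
- State from when reaction time is measured and when a key press is accepted.
- Read neutral-versus-emotion contrasts with caution even then. After a neutral first word, same is correct 122 times and different 61 times, a 2:1 expectation that favours fast neutral responses.

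No new data are needed, because order is known for every trial. The cost is precision: 10% of 244 is about 24 trials per emotion, and half of that, about 12, remain in the main analysis. Putting emotional-emotional pairs into the identical half would mean an emotional first word no longer settles the answer, but it changes the task and is not required for this correction.
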